### Methods in analysis to handle protocol non-adherence and any statistical methods to handle missing data {20c}

We will conduct both per-protocol and intention-to-treat analyses. We will conduct a sensitivity analysis excluding participants in the IM and IV tranexamic acid groups who did not receive tranexamic acid. Because we expect missing data to be minimal, we will summarise missing data for baseline and outcome variables but will not use any methods to impute it.

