##### Drug administration and dosage schedule

Women will be randomly allocated to receive:

i)1 g tranexamic acid as 2 × 5 ml IM injections (100 mg/ml) and slow IV injection of placebo (1 × 10 ml of 0.9% sodium chloride)ii)1 g tranexamic acid by slow IV injection (1 × 10 ml) and 2 × 5 ml IM injections of placeboiii)Placebo by 1 × slow 10-ml IV injection and 2 × 5 ml IM injections

In caesarean births, the trial treatment will be given prior to skin incision, immediately after draping. In vaginal births, the trial treatment will be given at crowning. There should be no delay in administering the trial treatment. Both IM injections should be given first, then the IV injection.

For IM administration, the 1 g dose (10 ml) is divided into two 5-ml IM injections to reduce the injection volume (5 ml is considered the upper limit) [22]. The IM injections should be given into the vastus lateralis, ventrogluteal region or deltoid. The vastus lateralis is the preferred site because it is a large muscle with no major nerve structures [23].

Each treatment pack contains clearly labelled IM and IV treatments. The IM treatment kit has two ampoules each containing 500 mg (5 ml) of TXA or placebo and two syringe labels. Two sterile 5-ml syringes and two needles will be provided. The IV treatment kit has two ampoules each containing 500 mg (5 ml) of TXA or placebo and one syringe label. One sterile 10-ml syringe and one needle will be provided. Before administration of IM and IV treatments, the expiry dates should be checked and the randomisation number confirmed. Appropriately qualified staff will prepare and administer the IM treatment first then the IV treatment:

IM treatment: Open the IM treatment kit and draw up the contents of each ampoule into each 5-ml syringe using the needles provided. Administer the two 5-ml IM injections first.

IV treatment: Open the IV treatment kit and draw up the contents of both ampoules into one 10-ml syringe using the needle provided. Administer one 10-ml injection as a slow intravenous injection at a rate of about 1 ml/min using the usual IV administration procedure, after administering the two IM injections.

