#### Criteria for discontinuing or modifying allocated interventions {11b}

If any contraindication to the trial treatment develops after randomisation, the trial treatment should be stopped.

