#### Strategies to improve adherence to interventions {11c}

Site investigators should record the date and time of trial treatment administration. If the trial treatment is not given, or is given outside of the prescribed period, a reason should be given. Adherence to the protocol will be monitored, and we will record whether the full dose was given.

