#### Implementation {16c}

Once a woman is confirmed to be eligible, just prior to skin incision in caesarean section births (after draping), or at crowning in vaginal births, a treatment pack will be taken from a box of packs by a delegated member of the research team. The woman is considered to have been randomised once administration of the first IM injection has started. Each site will keep a log of women they enrol in the trial.

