## Statistical methods

### Statistical methods for primary and secondary outcomes {20a}

We will draft a statistical analysis plan (SAP) for use by the Data Monitoring Committee (DMC) during their ongoing review. The SAP will be finalised before the trial database is locked for the final analysis.

The primary analysis comparing IM and IV tranexamic acid will be a per-protocol analysis. The analysis comparing tranexamic acid to placebo will be an intention-to-treat analysis. We will analyse the data and present statistics by randomised group. We will tabulate demographic and other baseline characteristics. Descriptive statistics for continuous variables will include the mean, standard deviation, median, range, and the number of observations. We will present categorical variables as numbers and percentages. Effect measures will be relative risk. Precision will be quantified using 95% confidence intervals. We will use the composite strategy to account for intercurrent events that may preclude the measurement of key efficacy and safety outcomes (e.g. early death, surgical interventions, discharge, or transfer to another hospital).

To compare the IV and IM routes of administration, we need to prespecify a non-inferiority margin—a predetermined margin of difference that is clinically acceptable. Women often experience treatment delays while waiting for a doctor or travelling to the hospital. Because tranexamic acid’s effectiveness falls by about 10% for every 15-min delay, a 1-h treatment delay corresponds to a 40% reduction in effectiveness. If IM administration preserves 60% of the benefit achieved with IV administration, IM tranexamic acid would be equivalent to an IV injection with a 1-h delay. An effect of this size from a more accessible route of administration with potentially fewer side effects would be clinically relevant. A 60% preservation fraction corresponds to a relative risk between IM and IV tranexamic acid of 1.13. If the upper limit of the two-sided 95% confidence interval for IM versus IV tranexamic acid is less than 1.13, then evidence of non-inferiority will have been provided.

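### The sensitivity analysis that drops women who did not receive tranexamic acid can remove almost only IV-arm women, so its groups are no longer comparable

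*Protocol article*

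**What the plan says.** All references are to the protocol article.

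- Section {20c}, on non-adherence and missing data, commits to per-protocol and intention-to-treat analyses and then adds: "We will conduct a sensitivity analysis excluding participants in the IM and IV tranexamic acid groups who did not receive tranexamic acid". It does not say which comparison this analysis serves. It has no matching exclusion for placebo, and it does not say whether a part dose or non-trial tranexamic acid counts as receipt.
- Section {16c}, Implementation: "The woman is considered to have been randomised once administration of the first IM injection has started".
- Drug administration and dosage schedule: "Both IM injections should be given first, then the IV injection". For the IV part: "Administer one 10-ml injection as a slow intravenous injection at a rate of about 1 ml/min". This order holds in all three arms, because each woman gets two IM injections and one IV injection.
- Section {11b}: "If any contraindication to the trial treatment develops after randomisation, the trial treatment should be stopped".
- Section {11c}, on adherence: "we will record whether the full dose was given".
- Section {20a}: "The primary analysis comparing IM and IV tranexamic acid will be a per-protocol analysis", and "The analysis comparing tranexamic acid to placebo will be an intention-to-treat analysis". Non-inferiority is judged by whether the upper 95% confidence limit lies below 1.13.

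**The concern.** The exclusion depends on receipt of the active drug, and the active drug arrives at a different step in each arm. In the IM arm it is in the injection whose start defines randomisation. In the IV arm it is in the last injection. Pack errors aside, an IM-arm woman cannot meet the exclusion criterion, while an IV-arm woman meets it whenever the IV part is not started.

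The women removed from the IV arm have counterparts in the IM and placebo arms who also missed the IV part, and those counterparts stay in. If missing the IV part is related to PPH risk, the contrast mixes a route effect with a difference in case mix. A sensitivity analysis is meant to show whether the main result is robust. This one could disagree with the main result, or agree with it, because of how its set is built.

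**Working it through.** **The plan's own yardstick.** Placebo risk is 0.115 and the assumed effect is RR 0.75, so risk on tranexamic acid is 0.115 × 0.75 = 0.08625. The benefit is 0.02875, and 60% of it is 0.01725. The margin is (0.115 − 0.01725) / 0.08625 = 1.133, which agrees with the stated 1.13.

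**Who can be excluded.** At the moment of randomisation an IM-arm woman has started active drug, and an IV-arm or placebo woman has started IM placebo. The IV part takes about 10 ml ÷ 1 ml/min = 10 min and follows both IM injections. If it is never started, the IM-arm woman stays in the set, the IV-arm woman leaves it, and the placebo woman stays.

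**Size of the shift, IM versus IV.** Let m be the share of women who would miss the IV injection in any arm, and k their PPH risk relative to the other women. Assume the two routes are equally effective. If the others' risk on drug is r, the IM-arm risk is r(1 − m + mk). The IV-arm risk after exclusion is r. Hence the expected RR is 1 + m(k − 1).

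| m | k = 0.5 | k = 1 | k = 2 | k = 3 |
|---|---|---|---|---|
| 0.5% | 0.998 | 1.000 | 1.005 | 1.01 |
| 1% | 0.995 | 1.000 | 1.01 | 1.02 |
| 2% | 0.99 | 1.000 | 1.02 | 1.04 |
| 5% | 0.975 | 1.000 | 1.05 | 1.10 |

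Both m and k are assumptions, because the article gives neither.

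**IV versus placebo in the same set.** Placebo keeps its women who missed the IV part, so the expected RR is 0.75 / (1 + m(k − 1)) instead of 0.75. At m = 5% this is 0.75 / 1.10 = 0.68 for k = 3 and 0.75 / 0.975 = 0.77 for k = 0.5. At m = 1% it is 0.74 and 0.75.

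**Non-trial tranexamic acid.** Women who develop PPH may be given it. If that counts as receipt, whether a woman is excluded depends on the outcome. Suppose 3% of IV-arm women miss the IV part, their risk is 11.5%, and all who bleed are treated with tranexamic acid. The retained IV-arm risk is (0.97 × 0.08625 + 0.03 × 0.115) / (0.97 + 0.03 × 0.115) = 0.08711 / 0.97345 = 0.0895. The IM/IV ratio is then 0.08625 / 0.0895 = 0.964. Under intention-to-treat it is 0.08625 / 0.08711 = 0.990.

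**If the same rule were used for a non-inferiority decision.** The article does not say that it is; these figures only show why it should not be. The article does not give the allocation ratio, so 10,000 per arm is assumed. The standard error of the log RR is √[(1 − p_IM)/(n_IM p_IM) + (1 − p_IV)/(n_IV p_IV)].

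- No exclusions: SE 0.0460, and power against 1.13 is Φ(0.1222/0.0460 − 1.96) = 76%.
- m = 2%, k = 3: p_IV = 0.08625/1.04 = 0.0829, n_IV = 9,800, SE 0.0468. Power is Φ((0.1222 − 0.0392)/0.0468 − 1.96) = 43%.
- m = 5%, k = 0.5, true ratio at the margin, SE (0.0463) kept at the equal-route rates: one-sided error is Φ(0.0253/0.0463 − 1.96) = 7.9% instead of 2.5%.

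**The symmetric alternative.** Dropping women who missed the IV part from every arm leaves risk r in both active arms, so the expected RR is 1.000 for every m and k in this model.

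**The case against.** A reader might infer that the primary non-inferiority analysis is biased. The article does not support that. The criticised sentence describes a sensitivity analysis with no named comparison, and it stands apart from the commitment to per-protocol and intention-to-treat analyses. Nothing says the per-protocol set is built on receipt of active drug. The adherence items recorded (full dose, timing) describe the whole kit and apply alike in every arm. An article may leave the definition of the per-protocol set to the SAP, so its absence here is no fault.

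Nor can the bias be asserted as fact. It needs a link between missing the IV part and PPH risk. The article's only stated ground for stopping treatment is a contraindication arising after randomisation. A link is plausible, since the IV injection runs for about 10 minutes around the birth or incision, but its direction and strength cannot be read from the text. With 1% or fewer missed, the shift is small against 1.13.

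An intention-to-treat analysis, which keeps everyone, is already planned. Whether it should carry weight in the decision is partly a separate preference.

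All of this stands, and it limits severity. It does not touch the structural point: the exclusion rule is stated, names only the two active arms, and by the protocol's own sequence of steps falls on one of them.

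**Conclusion.** The one-sidedness follows from the article's own text and needs no outside assumption. In the set as written, the IM versus IV and tranexamic acid versus placebo contrasts are not between comparable randomised groups.

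The size of the resulting bias is unknown. On assumed values it runs from nothing (k = 1) to an RR of 0.975 to 1.10 at 5% missed, and stays within 0.995 to 1.02 at 1% missed, for k from 0.5 to 3. It counts against IM if the missed women are at higher risk and in its favour if they are at lower risk. The power and error figures would apply only if the rule were carried into the per-protocol set, which the article does not say. Severity is minor to moderate: a badly fixed rule that is easily replaced, with no demonstrated threat to the primary conclusion.

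**What to change.** 1. Name the comparison that the sensitivity analysis serves.
2. Define its set, and the per-protocol set, by receipt of the full double-dummy trial treatment (both IM injections and the IV injection). Apply this identically in all three arms and blind to allocation. Do not define either set on receipt of the active component.
3. State that non-trial tranexamic acid does not count as receipt.
4. Report the already planned intention-to-treat IM versus IV analysis against the same 1.13 margin, as a check that must agree before non-inferiority is claimed. The two analyses complement each other. In the model above, untreated IV-arm women pull intention-to-treat towards IM: the RR is 0.75(1 − m + mk) / (0.75(1 − m) + mk), or 0.992 to 0.957 at m = 5% for k = 0.5 to 3. The kit-based set avoids this, but it relies on blinded staff omitting the IV part equally often, and in similar women, in every arm.

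The cost is SAP wording, settled before unblinding. Full-dose data are already to be recorded; the only check needed is that the form separates the IM and IV parts. The set loses a few women from every arm. With 9,500 instead of 10,000 per arm (5% missed, k = 1), the SE rises from 0.0460 to 0.0472 and power against 1.13 falls from about 76% to Φ(0.1222/0.0472 − 1.96) = 73%. Requiring agreement with intention-to-treat costs a little more, which was not computed.

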### Trial design {8}

The I’M WOMAN trial is a parallel, randomised, double-blind, placebo-controlled, three-arm trial comparing the effects of tranexamic acid by the intramuscular and intravenous route with placebo in women with one or more risk factors for PPH giving birth vaginally or by CS. About 30,000 women will be allocated to receive either (a) 1 g of tranexamic acid as two 5-ml IM injections (100 mg/ml) and IV placebo (10 ml 0.9% sodium chloride), (b) 1 g of tranexamic acid by IV injection and two 5-ml IM placebo injections, or (c) matching placebo. An optimal, allocation ratio was used to maximise study power.

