#### Relevant concomitant care permitted or prohibited during the trial {11d}

All women should receive the usual care in labour and after birth. There is no restriction on the use of concomitant medication. Participation will not result in any needed treatment being withheld. Women who develop PPH should be treated in the usual way at their hospital, which may include tranexamic acid.

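### The non-receipt sensitivity analysis excludes women only from the tranexamic acid groups, in effect almost only from the IV group, and can bias whichever comparison it serves

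*Protocol article*

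**What the plan says.** The rule stands in the protocol article, section {20c}: "We will conduct a sensitivity analysis excluding participants in the IM and IV tranexamic acid groups who did not receive tranexamic acid". It gives no matching exclusion for placebo. It does not name the comparison it serves, say how much drug counts as receipt, or say whether tranexamic acid from outside the trial counts.

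Other sections determine whom the rule can reach:

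- Implementation {16c}: "The woman is considered to have been randomised once administration of the first IM injection has started".
- Drug administration and dosage schedule: "Both IM injections should be given first, then the IV injection". The IV injection is 10 ml given "at a rate of about 1 ml/min using the usual IV administration procedure", so it lasts about 10 minutes.
- Trial design {8}: the IV group receives "tranexamic acid by IV injection and two 5-ml IM placebo injections". Its only trial drug is therefore in the last injection.
- Strategies to improve adherence {11c}: "If the trial treatment is not given, or is given outside of the prescribed period, a reason should be given", and "we will record whether the full dose was given".
- Concomitant care {11d}: "Women who develop PPH should be treated in the usual way at their hospital, which may include tranexamic acid".

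Under Statistical methods {20a}, the primary IM versus IV comparison is per protocol, and tranexamic acid versus placebo is by intention to treat.

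**The concern.** In the IM group the injection that makes a woman count as randomised already contains tranexamic acid. Barring a kit error, she cannot then fail to receive any. In the IV group, a woman whose IV injection is omitted has had no trial drug and is excluded. IM or placebo women for whom the same step was omitted are kept, although the double-dummy design shows the omission equally in every arm.

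The exclusion also depends on what happens after the first injections. In vaginal births the roughly 10-minute IV injection begins only after two IM injections given at crowning, and the Background says that PPH usually follows soon after birth. A link between missing the injection and bleeding is plausible, though the documents do not show one. If it exists, an analysis meant to test robustness to non-receipt sets a selected IV group against unselected IM or placebo groups.

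**Working it through.** **Inputs from the protocol.** Placebo risk 11.5%; relative risk (RR) 0.75, so the tranexamic acid risk is 0.115 × 0.75 = 8.625%; preservation fraction 60%; margin 1.13.

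**The plan's own figure.** Margin = (11.5 − 0.6 × 2.875)/8.625 = 9.775/8.625 = 1.133, which agrees with 1.13.

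**Assumptions, since the documents give neither.** A share f of every arm misses the IV injection, active or dummy. The PPH risk of these women is k times a reference. IM and IV are truly equal, and IM:IV is 1:1 for pooling.

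**Model A: k is relative to the arm average, with 8.625% in all randomised IM and IV women.** Excluding from the IV arm only:

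- IV risk = 0.08625 × (1 − fk)/(1 − f)
- IM/IV = (1 − f)/(1 − fk)
- pooled RR versus placebo = 0.75 × (2 − fk)/(2 − f)

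At f = 5%, k = 3: IV risk = 0.08625 × 0.85/0.95 = 7.72%; IM/IV = 0.95/0.85 = 1.12; pooled RR = 0.75 × 1.85/1.95 = 0.71.

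**Model B: k is the underlying risk relative to the other women, and IV women who miss the injection also lose the drug's benefit.** With c = 1 + f(k − 1), the IV women kept have risk 0.08625/c, so:

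- IM/IV = c
- pooled RR = 0.75 × [1 + (1 − f)/c]/(2 − f)

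| f | k | IM/IV, A | pooled RR, A | IM/IV, B | pooled RR, B |
|---|---|---|---|---|---|
| 1% | 2 | 1.01 | 0.746 | 1.01 | 0.746 |
| 2% | 3 | 1.04 | 0.735 | 1.04 | 0.736 |
| 5% | 2 | 1.06 | 0.731 | 1.05 | 0.733 |
| 5% | 3 | 1.12 | 0.712 | 1.10 | 0.717 |
| 5% | 1 | 1.00 | 0.750 | 1.00 | 0.750 |
| 5% | 0.5 | 0.974 | 0.760 | 0.975 | 0.759 |

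**Effect on the confidence limit.** In model B at f = 5%, k = 2, with 30,000 women assumed split 2:2:1 (IM:IV:placebo), the chance that the upper limit falls below 1.13 is 0.40. With 5% of the IV group excluded and no bias it is 0.82.

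**Same exclusion in all arms.** Every arm's risk is multiplied by the same factor, so IM/IV stays at 1.00 and tranexamic acid versus placebo at 0.75 for every f and k. This assumes that f and k are the same in each arm.

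**If non-trial tranexamic acid counted as receipt.** Suppose every woman with PPH is given it. IV women who missed the injection are then excluded only if they had no PPH. With f = 5%, and those women at the placebo risk of 11.5% (k = 1 in model B):

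- events kept = 0.95 × 0.08625 + 0.05 × 0.115 = 0.08769
- women kept = 0.95 + 0.00575 = 0.95575
- IV risk = 9.17%; IM/IV = 8.625/9.17 = 0.94
- pooled RR = [(0.08625 + 0.08769)/1.95575]/0.115 = 0.773

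Selection is now on the outcome, and the error favours IM.

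**The case against.** A reader might infer that the rule biases both comparisons, makes IM look worse and inflates the effect against placebo. The documents do not support that. There is no bias at k = 1, and it reverses at k below 1 or if non-trial drug counts as receipt. Section {20c} names no comparison; naming only the IM and IV groups is natural for an IM versus IV check, and then no placebo asymmetry arises. At f = 5%, k = 3, IV alone against placebo would give 7.72/11.5 = 0.67, but the protocol states the comparison as tranexamic acid against placebo, which gives 0.71. That case also puts 15% of IV-arm PPH in 5% of its women, which nothing in the protocol supports.

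Model A can be faulted for treating a missed drug as costless. With f = 5% and no selection, IV risk by intention to treat is 0.95 × 8.625% + 0.05 × 11.5% = 8.77%, so IM/IV is 0.98, and the one-sided exclusion returns it to 1.00. That is correct. Model B allows for this loss and still gives 1.05 to 1.10 at f = 5% with k of 2 to 3.

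That only IV women can be removed depends on the any-dose reading. A full-dose reading could remove IM women, as could treatment recorded as not given under {11c}. Either way, placebo women are never excluded.

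Finally, non-inferiority is decided per protocol and superiority by intention to treat, so no decision rule uses this analysis. That stands and limits the weight of the point.

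**Conclusion.** The one-sided exclusion is real. It follows from a stated rule, not from a detail left to the statistical analysis plan. With receipt read as any trial tranexamic acid, the rule removes essentially only IV-group women who missed the IV injection. It can bias whichever comparison it serves if missing that injection is related to PPH risk.

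Size and direction are open. Over the values tried in models A and B, IM/IV runs from 0.97 to 1.12 when the truth is 1.00, and pooled tranexamic acid versus placebo from 0.71 to 0.76 when the truth is 0.75. These are illustrations resting on assumed f, k and a 1:1 IM:IV ratio, not estimates. The primary analyses and the stated power of almost 90% are unaffected. This is an inexpensive improvement to a secondary analysis.

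**What to change.** Replace the rule with one receipt criterion that needs no knowledge of allocation: all IM and IV trial injections given. Apply it identically in every arm compared, including placebo wherever placebo is a comparator. Name the comparison or comparisons served, state that non-trial tranexamic acid does not count as receipt, and report the result beside the intention-to-treat result.

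Make sure the adherence record under {11c} captures IM and IV receipt separately; the article promises only a record of whether the full dose was given. Reconcile {11c}, which allows for treatment not given, with the definition of randomisation in {16c} and the exclusion in {20c}.

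The cost is about one sentence, and possibly a data field if separate receipt is not already recorded. A few more women leave a secondary analysis, which may overlap with the per-protocol set. The exclusion would still be made after randomisation: it removes the one-sidedness but does not guarantee freedom from bias if f or k differs between arms.
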